#### Screening and Baseline Survey

Potential participants who do not opt-out will then be sent an SMS message with a link to a survey. The survey will begin with a short eligibility screening section. Individuals who are screened out will be thanked for their time and informed that they do not meet the criteria for participating in the study.

Individuals who are not screened out will be directed to the consent cover letter and the remainder of the baseline survey. The baseline survey will collect information about demographics (age, sex, race/ethnicity, education, socioeconomic status), diabetes-related knowledge (11 items), and beliefs about the controllability of risk for type 2 diabetes (4 items) using 2 subscales on the risk perception for developing diabetes scale [25]. It will also collect information on self-efficacy related to DPP LCP participation as well as for diet, exercise, and weight loss (16 items) using the brief self-efficacy scales adapted from Wilson et al [26]. This will be followed by an 18-item scale of risk perceptions for T2DM that includes 6 items each to assess 3 different aspects of risk perception: deliberative, affective, and experiential risk perceptions [27].

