We will use logistic regression to compare the effects of the 3 treatments on the likelihood of enrollment and 1-month engagement in the DPP LCP. The distributions of participants’ demographics and baseline measures of risk perception and self-efficacy will be summarized and compared by treatment groups using chi-squared tests for categorical variables and *F* tests for continuous variables. If participants’ demographics and baseline measures of risk perception are not balanced across the 3 treatment groups at baseline, we will use inverse probability of treatment weighting with propensity scores to create a synthetic sample and compare the difference in the causal average treatment effects across the 3 treatment groups [35]. We will calculate standardized differences to check whether the distribution of baseline covariates is independent of treatment groups conditional on the propensity score. We will conduct intention-to-treat analysis to account for noncompliance. We will summarize missing data for all variables in the dataset. We will employ multiple imputation to examine the impact of any missing values in a sensitivity analysis. All analyses will be conducted using statistical programming language R, and statistical significance will be defined at alpha=.05.

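### Chance baseline imbalance, with no stated criterion, decides whether the primary comparison is plain logistic regression or propensity weighting

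*Protocol article*

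**What the plan says.** Under Statistical Analyses, Aim 1, the protocol article states the primary model: "We will use logistic regression to compare the effects of the 3 treatments on the likelihood of enrollment and 1-month engagement in the DPP LCP". Next, "participants’ demographics and baseline measures of risk perception and self-efficacy will be summarized and compared by treatment groups"; the tests are chi-squared for categorical and F for continuous variables. The following sentence is the switch; its condition names demographics jointly with risk perception: "baseline measures of risk perception are not balanced across the 3 treatment groups at baseline, we will use inverse probability of treatment weighting". The weights are to come from propensity scores, and the aim is to compare average treatment effects between the three arms. The section closes with "statistical significance will be defined at alpha=.05".

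Three features of that text matter here.

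- It gives no threshold for imbalance. Standardized differences appear only as a check conditional on the propensity score, after weighting has been chosen.
- It does not say whether the weighted or the unweighted result is primary. Multiple imputation, in the same section, is labelled a sensitivity analysis; weighting is not.
- Self-efficacy is among the variables tested but is not in the trigger.

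Allocation to Condition describes permuted blocks stratified by health system and sex, in a 1:2:2 ratio. Neither factor is named in the Aim 1 model.

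**The concern.** Under valid randomization a significant baseline difference is a chance finding, so these tests cannot show that the randomized comparison needs repair. Their p-values depend on the size of the imbalance and the sample size, and carry no information on whether the variable predicts enrollment. As a switch, the rule can reweight the trial because of an irrelevant variable and leave a strong predictor unadjusted because its p-value fell above the threshold. Baseline self-efficacy shows the gap: the protocol hypothesizes self-efficacy as the MAPS mechanism, yet an imbalance in it triggers nothing.

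At stake is which estimate counts as the primary result. The two routes also differ in what they report: a logistic regression effect on one, a weighted average treatment effect on the other. With no threshold and no ranking of the two, the choice falls to whoever judges balance.

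**Working it through.** **1. The plan's own figure.** The stated power is above 99% for 80 versus 160 participants at 2% versus 32% and 2% versus 45% (Sample Size and Power Calculation). Normal approximation, two-sided 0.05, for 2% versus 32%:

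- Pooled rate = (80×0.02 + 160×0.32)/240 = 0.22
- SE under the null = √(0.22×0.78×(1/80+1/160)) = 0.0567
- SE under the alternative = √(0.02×0.98/80 + 0.32×0.68/160) = 0.0401
- z = (0.30 − 1.96×0.0567)/0.0401 ≈ 4.71, so power is about 99.9999%

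For 2% versus 45% power is higher still. The stated figure reproduces, and nothing below changes it.

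**2. Variables in the trigger.** Screening and Baseline Survey names five demographics: "demographics (age, sex, race/ethnicity, education, socioeconomic status"). It measures "3 different aspects of risk perception: deliberative, affective, and experiential risk perceptions", which are three scales. That makes 5 + 3 = 8 variables, or 7 if sex is left out because stratification keeps it close to balanced.

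**3. Chance that the switch is thrown.** Assumption, not in the protocol: imbalance means p<0.05 on any one variable. With k independent tests under randomization, P = 1 − 0.95^k.

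| k | Variables | P, independent tests |
|---|---|---|
| 7 | without sex | 30.2% |
| 8 | with sex | 33.7% |

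**4. Correlated scales.** A simulation with arms of 80/160/160, F and chi-squared tests, 6,000 replicates per setting and an assumed correlation of 0.3 to 0.7 among the risk-perception scales gave 28% to 30% for 7 variables and 31% to 33% for 8. The overall range is therefore 28% to 34%.

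**5. Strict reading of the word joining demographics and risk perception.** If at least one variable in each group must be unbalanced, still at p<0.05 and with independent tests:

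- With sex: (1 − 0.95^5)×(1 − 0.95^3) = 0.226×0.143 = 3.2%
- Without sex: (1 − 0.95^4)×(1 − 0.95^3) = 0.186×0.143 = 2.6%

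Two readings of one sentence thus give trigger rates of about 30% and about 3%. A standardized-difference cut-off would give another rate.

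**6. Type I error of the two-step rule.** Null simulation at 80/160/160: eight independent normal covariates, any F-test p<0.05 switches to weighting, best practice versus one arm, robust variance with weights treated as known, 3,000 replicates per setting. Assumed enrollment rates were 2%, 10% and 30%, with prognostic effects from none to strong. Rejection, always-unweighted versus two-step, in six settings: 7.9% vs 7.9%, 3.7% vs 3.6%, 3.8% vs 3.9%, 4.9% vs 5.0%, 4.9% vs 4.5%, 4.7% vs 3.3%. A separate simulation (about 30% enrollment, one strong predictor, 1,500 runs) gave 4.6% vs 4.1%. The two-step rule adds no material inflation. The 7.9% arises at the 2% rate, where events are sparse, and the unweighted test shares it.

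**The case against.** The strongest reply has four parts.

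*The protocol never says p<0.05 is the criterion.* That is correct. It is the natural reading, because the tests come in the sentence before the switch and alpha=.05 is the only threshold in the section, but it is an inference, and the 28% to 34% depends on it.

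*Thresholds and covariate lists may sit in an analysis plan that is not shown.* This is fair, and their absence is not the point. The conditional switch itself is written here, and a threshold elsewhere would still leave chance to pick the estimator.

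*The switch uses baseline data, not outcomes, so the error rate is safe.* This largely stands. A reader might infer that an unaccounted selection step inflates the false-positive rate; the simulations do not support that. The protection against outcome-driven choice does, however, require that balance be defined in advance.

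*The practical effect is small.* At 2% versus 32% or 45% the significance verdict would rarely change. This stands too.

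Two stronger readings also fail. One might say that the switch is thrown in nearly half of trials: 11 or 12 tests give 43% or 46%. Reaching that count means adding the four self-efficacy domains, which are outside the trigger. One might also say that weighting would distort the control rate, since only 0.02×80 = 1.6 control enrollees are expected. With 2 enrollees in 80, weights of 0.6 or 1.8 on both would move 2.5% to about 1.5% or 4.5%. But that places both people at the same extreme of the weights, and 4.5% is still far from 32%. Sparse control events trouble any estimator and are a separate matter.

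**Conclusion.** The concern holds in a limited form. The protocol lets chance baseline imbalance choose between two estimators for the primary outcomes of a stratified randomized trial. It sets no criterion for imbalance and does not say which result is primary. Under a rule of p<0.05 on any one trigger variable, weighting would be used in about 3 of 10 trials (28% to 34%, depending on correlation and on whether sex counts). If both groups of variables must be unbalanced, it would be about 3%. That the text allows such different rates is part of the defect.

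The cost is an estimator not fixed in advance, room for discretion, and precision given up when prognostic or stratification variables are left out of the model. The effect estimates are more exposed than the significance verdict, and more so if the true effects are smaller than hypothesized. The point should be corrected, but it does not threaten the trial's validity.

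**What to change.** - Remove the baseline significance tests and the conditional sentence. Describe baseline by arm with summary statistics and standardized differences.
- Fix one primary analysis for both primary outcomes: logistic regression on arm, health system and sex, plus any further baseline covariates named before data are compared by arm, used whatever the observed balance.
- Keep propensity weighting, if wanted, as a sensitivity analysis that is always run and is labelled as such.

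Optional: with about 1.6 control enrollees expected, a penalised (small-sample) fit is reasonable, but this fix does not depend on it.

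The cost is analysis wording only. Sample size, power, data collection and conduct are unchanged, and the share of trials in which chance picks the primary analysis falls to zero.

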#### Aim 1.2

To examine the mechanisms underlying the mobile 360° video by comparing changes in deliberative, experiential, and affective risk perceptions across study arms, we will calculate the changes in risk perception scores across all 3 treatment groups using the scoring procedures described by Ferrer et al [27]. We will then use Baron and Kenny's [36] procedure to determine if the efficacy of the mobile 360° videos is mediated by changes in affective and experiential risk perceptions as hypothesized. The Baron and Kenny procedure assumes that the mediating factor is also randomly assigned to individuals in addition to the randomized baseline intervention (ie, sequential ignorability). However, the sequential ignorability assumption may not hold in this study even after adjusting for observed covariates. The potentially unmeasured confounders for the association between mediating factors and outcome may lead to biased inference. To reduce such bias, we will also employ 2 alternative casual modeling approaches, the structural mean model [37] and principal stratification [38,39], to evaluate how the impact of mobile 360° videos on DPP enrollment is mediated by risk perceptions.

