#### Follow-Up Survey

The follow-up survey will be sent via text message to all participants 4 weeks after the baseline survey is completed. The survey will include all of the items described in the baseline survey (diabetes-related knowledge, beliefs about the controllability of diabetes, self-efficacy, and risk perceptions). The survey will conclude with a 9-item questionnaire about the practical barriers and facilitators that were relevant to choosing whether to enroll in the DPP LCP such as perceptions of the need for counseling to change one's lifestyle (which prior work suggests many individuals don't feel the need for) [28]; accessibility of the DPP LCP in terms of cost, location, time requirements, and scheduling [29]; and desire to participate in an online vs in-person DPP LCP [30,31]. This portion of the survey will provide space for free-text comments on each barrier and also ask for input on other barriers we did not anticipate. At the end of the follow-up survey, participants will be asked if they are willing to participate in a short phone-based semistructured interview about their experiences in the study. We will randomly select up to 40 individuals for these interviews; those who are interviewed will receive a US $20 electronic gift card.

We will use Qualtrics survey software for all questionnaires used in this study [32]. This platform allows us to automate the timing and delivery of each intervention component. This platform will allow us to assess the number of people contacted and the click rate of participants in each intervention component. Finally, the platform also provides a mechanism for participants to easily opt out of the trial at any time by responding “STOP” to any text message.

Each participant will be sent US $20 electronic gift cards upon completion of the baseline survey and follow-up survey (US $40 total for the study). To motivate completion of all study procedures, participants who complete both the baseline and follow-up questionnaires will be placed into a lottery for 1 of 5 US $100 electronic gift cards.

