#### Aim 1.3

To examine the mechanism of the MAPS intervention by comparing changes in DPP LCP–related self-efficacy across study arms**,** we will calculate the changes in self-efficacy across all 3 treatment groups using the scoring procedures described by Wilson et al [26]. We will then use a similar mediation procedure to the aforementioned to determine if the efficacy of MAPS is mediated by changes in self-efficacy for DPP LCP enrollment and engagement and self-efficacy for health behavior change as hypothesized [37]. Our hypothesis is that if MAPS increases participants’ self-efficacy, then enrollment in the DPP LPC will increase.

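### The mechanism aims compare change scores and use them as mediators without stating adjustment for the baseline score, which would improve precision and remove a measured confounder

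*Protocol article*

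**What the plan says.** The two mechanism analyses are Aims 1.2 and 1.3 in the Statistical Analyses section (numbered 1.1 and 1.2 under Aims and Objectives).

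- **Video, risk perception.** The aim is pursued "by comparing changes in deliberative, experiential, and affective risk perceptions across study arms", and the derivation is "we will calculate the changes in risk perception scores across all 3 treatment groups using the scoring procedures described". The analysis then asks whether the effect of the videos is "mediated by changes in affective and experiential risk perceptions as hypothesized".
- **MAPS, self-efficacy.** The wording is parallel: "we will calculate the changes in self-efficacy across all 3 treatment groups using the scoring procedures described", followed by a similar mediation procedure.
- **Covariates.** No model is named for the between-arm comparison and no baseline covariate is listed. Adjustment appears once in these two sections, in a caution about the mediation assumption: "the sequential ignorability assumption may not hold in this study even after adjusting for observed covariates". The covariates are not listed there.
- **Baseline scores elsewhere.** Under Aim 1, propensity-score weighting is used on a condition: "If participants’ demographics and baseline measures of risk perception are not balanced across the 3 treatment groups at baseline".
- **Data available.** Allocation follows completion of the baseline survey. Of the 4-week follow-up survey the article says "The survey will include all of the items described in the baseline survey". Each scale is therefore measured at both times.

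**The concern.** Comparing changes between arms with no baseline covariate amounts to fixing the slope of the week-4 score on baseline at 1. When that slope is below 1, subtracting the whole baseline score adds noise that a regression would leave out. The comparison is with a control arm planned at 80, and the article's power statement covers enrollment only, so precision on these scores is not known to be ample.

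The second issue concerns mediation. Randomization protects the arm-to-mediator path but not the mediator-to-outcome path. A change score is negatively correlated with its own baseline whenever that slope is below 1. If people with higher baseline risk perception or self-efficacy are more or less likely to enroll anyway, baseline is a common cause of mediator and outcome. It is a measured one, and the plan does not name it.

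**Working it through.** **1. The plan's own figure.** The only power figure is for enrollment: above 99%, with 80 versus 160, 2% versus 32% or 45%. A two-sided alpha of 0.05 is assumed, since the article does not state sidedness.

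- 2% vs 32%: pooled rate (1.6 + 51.2)/240 = 0.22. Null SE = √(0.22 × 0.78 × (1/80 + 1/160)) = 0.0567. Alternative SE = √(0.02 × 0.98/80 + 0.32 × 0.68/160) = 0.0401. z = (0.30 - 1.96 × 0.0567)/0.0401 ≈ 4.71, so power is 99.9999%.
- 2% vs 45%: the same steps give power above 99.9999%.

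The stated figure is reproduced. It says nothing about the mechanism scores, for which the article gives no power, SD or correlation.

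**2. Precision of the two comparisons.** Assumptions: equal SD σ at baseline and week 4, and correlation r between them. Per-person variance in units of σ²:

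- unadjusted change: 2(1 - r)
- week-4 score adjusted for baseline: 1 - r²
- ratio, adjusted to unadjusted: (1 - r²)/(2(1 - r)) = (1 + r)/2
- precision lost by not adjusting: 1 - (1 + r)/2 = (1 - r)/2

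Detectable differences use 80 vs 160, 80% power and two-sided 0.05: (1.960 + 0.842) × √(1/80 + 1/160) × √variance = 0.3836 × √variance. The power column is for unadjusted change at the difference where the adjusted analysis has 80%: Φ(2.802 × √((1 + r)/2) - 1.960).

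| r (assumed) | Variance, change | Variance, adjusted | Precision lost | SE larger by | Detectable difference, change → adjusted (SD) | Power, change |
|---|---|---|---|---|---|---|
| 0.3 | 1.40 | 0.91 | 35% | 24% | 0.454 → 0.366 | 62% |
| 0.5 | 1.00 | 0.75 | 25% | 15% | 0.384 → 0.332 | 68% |
| 0.7 | 0.60 | 0.51 | 15% | 8% | 0.297 → 0.274 | 73% |

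Over r = 0 to 0.9 the loss runs from 50% to 5%. A simulation of 4,000 trials of 80 vs 160 at each r gave variance ratios of 0.648, 0.749 and 0.846, against 0.65, 0.75 and 0.85 from the formula.

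**3. Unequal SDs.** If the week-4 SD is k times the baseline SD, the loss is 1 - k²(1 - r²)/(1 + k² - 2rk). For r = 0.3 to 0.7 this is 50% to 37% at k = 0.8, and 22% to 2% at k = 1.25.

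**4. Change with baseline as covariate.** If Y - B = a + τ·arm + βB, then Y = a + τ·arm + (β + 1)B. The arm effect τ is the same in both, and the simulation agreed to rounding error (about 10⁻¹⁵). What matters is whether baseline is in the model, not whether the outcome is written as a change.

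**5. Correlation of change with baseline.** With equal SDs, Cov(Y - B, B) = -(1 - r)σ² and SD(Y - B) = σ√(2(1 - r)). The correlation is therefore -√((1 - r)/2): about -0.59, -0.50 and -0.39 at r = 0.3, 0.5 and 0.7. The confounding this can cause in the mediator-outcome path also depends on how strongly baseline predicts enrollment, which the article does not give, so it cannot be sized here.

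**The case against.** The strongest reply is that the article nowhere says the changes will be compared unadjusted. The quoted sentences derive a variable and name no test. Baseline may be in the model, and then step 4 shows that nothing is lost. A condensed article may also leave a covariate list to the analysis plan. This stands in part: a reader might infer that the plan commits to raw change scores, and the text does not support that. It does make change both the between-arm measure and the mediator, and it names no baseline covariate for either.

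A second reply is that adjustment is already contemplated. The remark on observed covariates discusses an assumption and does not list the baseline score. The added structural mean model and principal stratification are aimed at unmeasured confounding, whereas the baseline score is measured. The weighting under Aim 1 depends on finding imbalance, and its trigger names risk perception but not self-efficacy, the MAPS mediator.

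Three further points stand and limit the claim:

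- A reader might infer that the change comparison is biased. Over randomizations it is not; it departs from the true effect only conditionally on an observed baseline difference.
- A reader might take the scales to be noisy. The article gives no reliability and calls its questionnaires validated under Strengths.
- The Abstract words the secondary hypotheses as associations of change with enrollment within the video group and within the MAPS group. A sharper between-arm comparison does not help those, although confounding by baseline applies to them as well.

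**Conclusion.** The point holds conditionally. If changes are compared without the baseline score as covariate, the mechanism comparisons remain unbiased over randomizations but lose precision: 35%, 25% and 15% at r = 0.3, 0.5 and 0.7 with equal SDs. It is tempting to quote 15% to 35% as a property of this trial. The documents do not support that, because the range rests on assumed correlations and an assumed equality of SDs, and it is on the variance scale; standard errors rise by about 8% to 24%. The confounding of the mediator-outcome path is a possibility that depends on baseline predicting enrollment. Enrollment and 4-week engagement, the primary outcomes, are not touched. This is a worthwhile correction to secondary analyses, not a threat to the trial's main conclusion.

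**What to change.** In Aims 1.2 and 1.3, state that:

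- each week-4 risk-perception and self-efficacy score (or, equivalently, its change) is regressed on arm, its own baseline score, and the stratification factors health system and sex;
- each intervention minus best practice is reported with a 95% CI;
- the baseline score of the mediator is included in both the mediator model and the outcome model of the mediation analysis.

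If this is already intended, one sentence saying so closes the point. The cost is wording only: the baseline items are already in the survey completed before allocation, and no procedure or sample size changes.

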### Measures

#### Outcome Measures

The primary outcomes of the study are DPP LCP enrollment and 4-week engagement, as defined by the CDC (Table 1). These data are currently collected by all CDC-recognized organizations offering the National DPP LCP and are a part of their required reporting for DPP LCP recognition.

**Table 1 table1:** Centers for Disease Control and Prevention (CDC)–defined measure of enrollment and engagement in in-person and online Diabetes Prevention Program’s Lifestyle Change Programs (DPP LCPs).

Time point	In-person	Online
Milestone 1 (enrollment)	Registration for the program	Setting their password for the app
Milestone 2 (4-week engagement)	Attending at least 2 out of the first 4 sessions	Must do at least 2 of the following activities: (1) Complete 2 education modules; (2) send at least 1 in-app message and/or Group Wall post; (3) set or log at least 1 behavior; (4) log, plan, or research at least 3 meals; (5) log physical activity at least 3 times; (6) weigh in on 3 or more days during 2 out of the first 4 sessions

The DPP LCP at University of Utah Health is covered by some insurance plans and requires an out-of-pocket fee for those without coverage. The cost for the online program is currently US $504, and the cost for the in-person program is US $425. Some scholarships are available for those who meet income guidelines. These costs may change during the course of the study. The Midvale CBC’s program is offered free of charge and is currently funded by a grant. To minimize the problem of cost as a barrier to enrollment, University of Utah Health participants who are uninsured or underinsured may be invited to participate in the Midvale CBC program. Otherwise, all other participants will only be invited to attend the program offered by their health system.

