### Statistical Analyses

#### Sample Size and Power Calculation

Statistical power for the primary analysis in Aim 1 was calculated using the statistical power calculation software PASS 14 [34]. Based on prior work on the effect of risk notification and education, we hypothesize that 2% of participants in the risk notification and education arm of the study will enroll in the DPP LCP. In the intervention arms, based on our pilot work, we hypothesize that enrollment in the DPP LCP will increase to 32% and 45% for the mobile 360° video and MAPS arms, respectively (manuscript for the video pilot study submitted to JMIR Diabetes, 11/26/20; manuscript for MAPS pilot in preparation). We plan for a total sample size of 400; of whom, 80 will be randomized to risk notification and education alone, 160 will be randomized to risk notification and education plus mobile 360° video, and 160 will be randomized to risk notification and education plus MAPS. We calculated that this study will have >99% power to detect the hypothesized differences between the best practice arm and the intervention arms. To address the possibility of loss to follow-up, we are planning to recruit a total of 480 individuals into the trial.

#### Aim 1

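### If the Baron and Kenny steps for enrollment are fitted by logistic regression, the drop in the treatment coefficient mixes mediation with rescaling and should not be read as mediation

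*Protocol article*

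**What the plan says.** Section numbers here follow the Statistical Analyses part of the protocol article.

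- Aim 1.2 (video): "We will then use Baron and Kenny's [36] procedure to determine if the efficacy of the mobile 360° videos is mediated". The mediators named are the affective and experiential components of risk perception. The section concedes that unmeasured confounding between mediator and outcome may bias this. For that reason it adds a structural mean model and principal stratification "to evaluate how the impact of mobile 360° videos on DPP enrollment is mediated by risk perceptions".
- Aim 1.3 (MAPS): "We will then use a similar mediation procedure to the aforementioned to determine if the efficacy of MAPS is mediated". The mediator there is self-efficacy.
- Outcome Measures, Table 1: enrollment is a yes/no milestone, "Registration for the program" for the in-person format and setting the app password for the online format.
- Aim 1: "We will use logistic regression to compare the effects of the 3 treatments on the likelihood of enrollment". The same model serves 1-month engagement. This is the only model the article names for enrollment. Aims 1.2 and 1.3 name no regression model for the Baron and Kenny steps.
- Sample Size and Power Calculation: "2% of participants in the risk notification and education arm of the study will enroll in the DPP LCP", and "enrollment in the DPP LCP will increase to 32% and 45% for the mobile 360° video and MAPS arms, respectively". Of the planned 400, "80 will be randomized to risk notification and education alone, 160 will be randomized to risk notification and education plus mobile 360° video", with a further 160 in the MAPS arm.

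**The concern.** One step of the Baron and Kenny procedure compares the treatment coefficient before and after the mediator enters the model and reads shrinkage as mediation. In a linear model that is sound. In a logistic model the coefficient also depends on how much outcome variation the other covariates explain (non-collapsibility). Adding a mediator that predicts enrollment therefore moves the treatment coefficient away from zero even when the arm has no effect on the mediator. Mediation moves it toward zero, and the two changes partly or wholly cancel.

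A small outcome probability would limit the rescaling, but the planned rates of 32% and 45% in the intervention arms are not small. The weakness the article acknowledges is confounding, which is a different problem.

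At stake is a secondary mechanism result: an analyst who relied on the shrinkage step could report little or no mediation by risk perception or self-efficacy when it is present.

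**Working it through.** **The plan's own figure.** Power for 80 versus 160 at 2% versus 32%, pooled z, alpha 0.05 taken as two-sided:
- pooled rate = (1.6 + 51.2)/240 = 0.22
- null SE = √(0.22 × 0.78 × (1/80 + 1/160)) = 0.0567
- alternative SE = √(0.02 × 0.98/80 + 0.32 × 0.68/160) = 0.0401
- z = (0.30 − 1.96 × 0.0567)/0.0401 ≈ 4.7, so power is about 0.999999

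The stated power above 99% is reproduced. It does not depend on the mediation analysis.

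**Inputs.** From the article: rates of 2%, 32% and 45%; arms of 80, 160 and 160. Assumed, because the article gives no mediator effects: arm effect on the mediator a = 0.2 to 0.5 SD, and mediator log odds ratio b = 0.5 to 1.5 per SD. One standardised mediator stands in for those named.

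**Model.** X is arm, M = aX + e with e ~ N(0,1), and logit P(Y=1) = i + c′X + bM. The values of i and c′ are solved by Gaussian quadrature so that the marginal rates equal the plan's.

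**Total coefficient.** c = logit(0.32) − logit(0.02) = −0.754 + 3.892 = 3.138 for video, and −0.201 + 3.892 = 3.691 for MAPS.

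**Decomposition.** In this model c − c′ = ab − r(b). The term ab is the mediated part on the logit scale. The term r(b) is pure rescaling, the amount by which the coefficient rises when a = 0:

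| b | r, video | r, MAPS |
|---|---|---|
| 0.5 | 0.077 | 0.108 |
| 1.0 | 0.315 | 0.426 |
| 1.5 | 0.708 | 0.930 |

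**True mediated share.** The natural indirect effect (NIE) is the intervention-arm rate minus the rate that arm would have with the control distribution of M. The share is the NIE divided by the risk difference. Video arm (2% versus 32%):

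| a | b | c′ | c − c′ | change in c | NIE, points | true share |
|---|---|---|---|---|---|---|
| 0.2 | 0.5 | 3.115 | 0.023 | +0.7% | 2.0 | 6.8% |
| 0.3 | 1.0 | 3.153 | −0.015 | −0.5% | 5.2 | 17.5% |
| 0.5 | 1.0 | 2.953 | 0.185 | +5.9% | 8.4 | 28.2% |
| 0.2 | 1.5 | 3.546 | −0.408 | −13.0% | 4.5 | 15.2% |
| 0.5 | 1.5 | 3.096 | 0.042 | +1.3% | 10.7 | 35.6% |

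Here a positive change is shrinkage, (c − c′)/c. Second row: ab − r = 0.300 − 0.315 = −0.015, so the coefficient does not shrink although 5.2 of the 30 points are mediated.

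**Ranges over a = 0.2, 0.3, 0.5 and b = 0.5, 1.0, 1.5:**

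| rates | true share | change in c |
|---|---|---|
| 2% vs 32% | 7% to 36% | −13% to +6% |
| 2% vs 45% | 5% to 29% | −17% to +4% |
| 10% vs 32% (assumed control rate) | 9% to 49% | −11% to +21% |

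In all 27 combinations the coefficient change understates the true share. For video, the drop is exactly zero at a true share of 5%, 18% and 34% for b = 0.5, 1.0 and 1.5. For MAPS the shares are 6%, 20% and 36%.

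**Sampling behaviour.** 1,500 simulated trials per scenario, 80 versus 160, 2% versus 32%, mediation real throughout:

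| a | b | logistic drop ≤ 0 |
|---|---|---|
| 0.3 | 1.0 | 53% |
| 0.3 | 1.5 | 82% |
| 0.5 | 0.5 | 1% |
| 0.5 | 1.0 | 12% |
| 0.5 | 1.5 | 44% |

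Across these scenarios the linear-probability drop was ≤ 0 in 0% to 1.4% of trials. The test of arm on mediator was significant in 56% to 96%, and the test of mediator on outcome in 82% to 100%.

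**Control events.** 80 × 0.02 = 1.6 expected, and 0.98^80 = 19.9% of trials would have none. The logistic treatment coefficient then has no finite estimate, and such trials were left out of the percentages above.

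**The case against.** - **The link is inferred.** Aims 1.2 and 1.3 name no regression model, and a condensed article may leave that to the full plan. This stands, and it is why the point is conditional. A reader might infer that Baron and Kenny fails for any binary outcome. It does not: the fault lies in the logit link, and with a linear probability model the drop equals the product of the two paths.
- **The procedure has other steps.** The tests of arm on mediator and of mediator on outcome given arm remain usable for detecting mediation under a logistic model. This stands too. What remains is that the shrinkage step belongs to the named procedure and could contradict two significant paths.
- **Other methods are planned.** The structural mean model and principal stratification give separate answers to the mediation question, so a false negative would not go unchallenged. They were added for confounding, however, and do not correct how a logistic coefficient change is read.
- **The sizes rest on assumptions.** They do. Failure is rare with a larger arm effect and a weak mediator (1% of simulated trials at a = 0.5, b = 0.5) and common in the reverse case.
- **Few control events are a separate matter.** They affect any logistic model of enrollment, including the one proposed below. They bear on how the replacement is fitted and are not part of the fault itself.

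**Conclusion.** The point holds conditionally. If the mediation steps in Aims 1.2 and 1.3 use the logistic model named for enrollment, the change in the treatment coefficient should not be read as mediation. At the planned rates and the assumed mediator effects it runs from −13% to +6% for video, where 7% to 36% of the risk difference is mediated, and from −17% to +4% for MAPS, where 5% to 29% is.

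A reader might go further and infer that the mechanism aims or the design of the follow-on trial turn on this drop. The article does not support that. Aims and Objectives frames the mechanism aims as comparing changes in risk perception and self-efficacy between arms. The Abstract frames the secondary hypotheses as associations between those changes and enrollment. Future Work already sets out the sequence of the later trial without tying any step to the mediation result. The primary comparison and its stated power are untouched.

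**What to change.** In Aims 1.2 and 1.3, state that a change in the logistic treatment coefficient will not be used as the criterion for mediation. Instead, estimate natural direct and indirect effects on the risk-difference scale, with:
- a linear model for the mediator;
- a penalised logistic model for enrollment, since only about 1.6 control enrollees are expected;
- bootstrap confidence intervals;
- a sensitivity analysis for unmeasured mediator-outcome confounding.

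At minimum, replace the shrinkage step by a joint test of the two paths. If a linear probability model was intended all along, one sentence saying so removes the problem. Keep the planned structural mean model and principal stratification.

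The cost is a few sentences and a little more analysis work in standard R software, with no new data. The limit is that natural effects still need sequential ignorability, which the article itself says may not hold. The sensitivity analysis probes that assumption but does not remove it.
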